### Study interventions

Two 5.25 ml blood samples will be taken from existing intravascular lines at two time-points: Sample 1, immediately following anaesthetic induction.Sample 2, *after* cessation of CPB, heparin reversal and other routinely performed interventions that may influence blood clotting such as cell saver return but *before* the start of the return of pump blood (see below).

The volume of the blood required may, in exceptional circumstances, be tolerated poorly by participants with small circulating volumes or critical cardiovascular function. In order to minimise the risk of harm to participants, the clinicians with responsibility for the participants will be instructed to consider the consequence of taking each blood sample on a case-per-case basis and will not take a blood sample if this is considered to be detrimental to the participant. The clinician will be asked to sign the case report (CRF) form to indicate they agree to each blood sample being taken.

### Primary outcomes

The primary outcome is clinical concern about bleeding. This outcome will be determined for the following time intervals:

Interval A: The period between sample 1 and sample 2

Interval B: The period between sample 2 and chest drain insertion.

Interval C: The first 12 h after chest drain insertion.

Clinical concern about bleeding is defined as:High blood loss. Chest drain volume of either >5 ml/Kg/hr in any 1 h interval or >3 ml/Kg/hr for 3 consecutive hours (Hazinski guidelines [7]) in interval C.ORAny non-routine pro-haemostatic treatment given in response to bleeding by the clinical team. This is defined as any of the following: protamine given after initial heparin reversal; fresh frozen plasma (FFP); cryoprecipitate; platelet concentrates; any anti-fibrinolytic drug; activated recombinant factor VII (rFVIIa); fibrin sealant or fibrinogen concentrate.

The composite endpoint is necessary because of two important constraints:Blood loss is readily quantified after chest drain insertion by measuring drain volume. However, in intervals A and B (before chest drain insertion), measurement of blood loss is not feasible.Non-routine pro-haemostatic therapies are usually given soon after the start of abnormal bleeding and, if effective, prevent further bleeding. Measuring only ‘high blood loss’ would result in the primary endpoint of excessive bleeding not being identified in these instances.

There are two other circumstances in which clinicians administer pro-haemostatic therapies during or after cardiac surgery in children:As part of our standard institutional protocols for all children in the study population. These are termed ‘routine’ pro-haemostatic therapies and include interventions such as cryoprecipitate infusion and the administration of protamine to reverse the effects of heparin at the end of surgery.In response to a perceived risk of excessive bleeding but before excessive bleeding starts. These are termed ‘non-routine prophylactic’ pro-haemostatic therapies and are usually given during interval B.

Clinicians will be asked to classify all pro-haemostatic treatments in the study intervals A-C into one of three categories i) ‘routine’, ii) ‘non-routine in response to bleeding’; or ‘non-routine prophylactic’ on the study CRFs. The ‘routine’ and ‘non-routine prophylactic’ pro-haemostatic treatments will not be considered part of the primary outcome.

In some children, blood from the CPB circuit (pump blood) is re-infused during interval B and C requiring additional protamine to be administered to reverse the heparin contained in this blood. We have considered this protamine dose to be part of the ‘routine’ management. Re-infusion of pump blood will be recorded on the CRF but the additional protamine will not be classified as part of the primary clinical outcome.

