## Background

Better blood and blood component transfusion is a longstanding NHS priority that is highly pertinent to cardiac surgery since the 40,000 cardiac surgery procedures in the UK each year account for 18 % of all NHS blood components used. This statistic includes 3,000 children who undergo cardiac surgery requiring cardiopulmonary bypass (CPB) and who have a 30-day mortality of 4 % and post-operative morbidity from organ injury or sepsis of about 25 % [1]. Excessive bleeding occurs in 40 % of children after cardiac surgery and is typically treated by transfusion of red cells and other blood components such as fresh frozen plasma, cryoprecipitate or platelet concentrates. However, in current NHS practice, a further 40 % of children receive blood components empirically at the end of surgery in an attempt to prevent excessive bleeding [2]. Decisions to administer blood components are not standardised and there is marked variation between NHS centres in the prevalence of excessive bleeding and in blood component use [2]. Excessive bleeding and transfusion of red cells or other components are independently associated with increased risk of post-operative morbidity and mortality arising from adverse events such as sepsis and kidney, brain and lung injury [1]. Adverse events have a significant impact on children and their families and substantially increases healthcare costs.

A major cause of excessive bleeding in children after cardiac surgery is abnormality in the blood clotting system. This is typically complex and multi-factorial and may be influenced by blood clotting abnormalities that pre-exist in the child. However, blood clotting is also affected by anaesthetic techniques that are essential for cardiac surgery to be performed. Therefore, blood clotting abnormalities vary markedly between children and change within individual children during the course of surgery [3–5]. Amongst the range of possible blood clotting abnormalities, low platelets and low fibrinogen have been most commonly observed in small single-centre or single-diagnosis groups of children and were associated with excessive bleeding [3–5]. Associations between these blood clotting abnormalities and excessive bleeding have not been tested in larger unselected cohorts.

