### Sample size calculation

The study size is 200 participants with blood samples taken. In estimating the power of the study and precision of the estimates, we have assumed that the rate of the primary outcome is 50 % in this population. Additionally, we have considered two alternative estimates of prevalence of blood clotting abnormalities (30 % and 5 %) in the study population:

**Objective 1** (describing the prevalence of different blood clotting abnormalities in the population): a sample size of 200 participants will allow a prevalence of 30 % to be estimated with a 95 % confidence interval of +/− 7 % (23.7 %, 36.9 %) and a prevalence of 5 % to be estimated with a 95 % confidence interval of +/− 4 % (2.4 %, 9.0 %).

**Objective 2** (estimating the extent to which TEM and reference laboratory test results predict clinical concern about bleeding): the power to estimate a relative risk of a given magnitude is dependent on the prevalence of the blood clotting abnormalities and increases with increasing prevalence. The study will have a minimum of 77 % power to estimate a relative risk of 1.5, given a rate of blood clotting abnormalities of >30 % in the population and >80 % power to estimate a relative risk of 2, given a rate of blood clotting abnormalities of between 4 % and 5 %.

**Objective 3** (estimating diagnostic accuracy of TEM test results vs. reference test results): a sample size of 200 participants will allow the sensitivity and specificity of each TEM test result to identify defined blood clotting abnormalities with a prevalence of 30 % to be estimated with a 95 % confidence interval of +/− 10 % (79.5 %, 96.2 %) for a sensitivity of 90 % increasing to +/−13 % (46.5 %, 72.4 %) for a sensitivity of 60 %. The specificity will be estimated with a 95 % confidence interval of +/−6 % (83.8 %, 94.4 %) for a specificity of 90 % increasing to +/−9 % (51.4 %, 68.2 %) for a specificity of 60 %. For a prevalence of 5 %, the 95 % confidence intervals are +/− 35 % (55.5 %, 100 %) for a sensitivity of 90 % and +/−35 % (26.4 %, 87.8 %) for a sensitivity of 60 %. The corresponding figures for specificity are +/− 5 % (84.8 %, 93.9 %) for 90 % specificity and +/− 7 % (52.7 %, 67.0 %) for 60 % specificity.

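### The primary outcome treats non-routine prophylaxis as a non-event in one place and as an event in the Abstract; under the non-event rule, effective and targeted prophylaxis would attenuate the objective 2 results by an unknown amount

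*Protocol article*

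**What the plan says.** All references are to the protocol article.

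- **Primary outcomes.** An event is high chest drain loss in interval C, or non-routine treatment given because the child is bleeding. Clinicians place every pro-haemostatic treatment in one of three categories on the CRF. The third category, non-routine prophylactic, is treatment given "In response to a perceived risk of excessive bleeding but before excessive bleeding starts"; such treatments "are usually given during interval B", which runs from sample 2 to chest drain insertion. Routine and non-routine prophylactic "pro-haemostatic treatments will not be considered part of the primary outcome".
- **Abstract, Methods/Design.** The composite is described as excessive blood loss, or treatment outside standard protocols given because the risk of excessive bleeding is thought to be high.
- **Background.** In NHS practice a further 40% "of children receive blood components empirically at the end of surgery in an attempt to prevent excessive bleeding".
- **Statistical analyses.** Objective 2 uses logistic regression of the primary outcome on individual test results, and ROC analyses to choose cut-offs. No role is described for treatment given between test and outcome.
- **Sample size calculation.** "The study size is 200 participants with blood samples taken", and "we have assumed that the rate of the primary outcome is 50 % in this population". For objective 2 the article claims a "minimum of 77 % power to estimate a relative risk of 1.5" when abnormality prevalence is above 30%.

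**The concern.** There are two linked problems.

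First, the same child is scored in opposite ways. A child given non-routine prophylaxis who never bleeds is an event by the Abstract and a non-event by the Primary outcomes section.

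Second, the Primary outcomes rule has a cost that the article does not discuss. Prophylaxis in interval B comes after sample 2 and before drain loss is measured, and it goes to children whom clinicians think likely to bleed. If it works, some children whose abnormal test was a correct warning are scored as having no clinical concern. If such children are also treated more often than children with normal tests, a good test loses true positives and gains apparent false positives. The article justifies its composite on the ground that successful treatment would otherwise hide cases, but it does not extend that thought to treatment given before bleeding.

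The study is meant to pick out the most useful TEM tests and to inform later randomised trials. A parameter that detects risk on which clinicians already act could be dropped for that reason.

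**Working it through.** **Step 1. Reproduce the stated power.** Inputs from Sample size calculation: N = 200, overall outcome rate 50%, abnormality prevalence 30% (60 abnormal, 140 normal), relative risk (RR) 1.5. Two-sided alpha of 0.05 is my assumption, since none is stated for the power figure.

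Risk in normal children = 0.50 / (0.7 + 0.3 × 1.5) = 0.50 / 1.15 = 43.5%. Risk in abnormal children = 1.5 × 43.5% = 65.2%. A pooled two-proportion test with continuity correction gives 76.7% power, which matches the stated 77% (81.3% without the correction). The stated figure is not itself in error.

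**Step 2. Effect of prophylaxis on the observed RR.** Let q be the share of children given non-routine prophylaxis, k the ratio of treatment probability in abnormal versus normal children, and r the proportion of bleeding prevented in treated children. None of the three is in the article, so all are assumptions.

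- Share treated among normal: t0 = q / (0.7 + 0.3k). Among abnormal: t1 = k × t0.
- Observed RR = 1.5 × (1 − t1·r) / (1 − t0·r).

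Example with q = 40%, k = 2, r = 50%: t0 = 0.4 / 1.3 = 0.308 and t1 = 0.615. Observed RR = 1.5 × 0.692 / 0.846 = 1.23.

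**Step 3. Power with the outcome rate held at 50%.** The article assumes 50% for this population under its usual care, so I keep that rate and change only the RR: risk in normal children = 0.50 / (0.7 + 0.3 × RR). With RR 1.23 the risks are 57.4% and 46.8%, and power by the Step 1 method is 23%.

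Results for k = 2:

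| Share treated (q) | RR, r = 30% | RR, r = 50% | Power, r = 30% | Power, r = 50% |
|---|---|---|---|---|
| 10% | 1.46 | 1.44 | 71% | 66% |
| 20% | 1.43 | 1.37 | 64% | 53% |
| 40% | 1.35 | 1.23 | 47% | 23% |

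With k = 1 (no targeting) the two factors cancel and the RR stays at 1.5. With r = 0 (no efficacy) nothing changes.

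**Step 4. Sensitivity.** The share of events found in abnormal children is 0.3 × RR / (0.7 + 0.3 × RR). At RR 1.5 this is 0.45 / 1.15 = 39.1%. At RR 1.23 it is 0.368 / 1.068 = 34.5%.

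**Step 5. The Abstract's coding is not neutral either.** If every treated child is an event and the others keep the Step 1 risks, observed risk = 1 − (1 − t)(1 − p), where p is the Step 1 risk. At q = 40% the RR is 1.42 with k = 2 and 1.20 with k = 1, and the event rate rises to about 69% and 70%. The outcome then partly measures clinicians' perception. Neither coding alone settles the matter, which is why both should be seen.

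**The case against.** The case against is substantial, and much of it stands.

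- **The 40% is not this study's figure.** A reader might infer that about 40% of participants will be given non-routine prophylaxis in interval B. The article does not say so. The 40% describes NHS practice generally and any blood component given empirically, and the Background notes marked variation between centres. This centre lists cryoprecipitate infusion among its routine treatments, so part of its empirical use may fall outside the category. The share here is unknown. This stands.
- **Lower power figures are available but unsupported.** Treating the stated 50% as a rate without prophylaxis, and then subtracting the treatment effect, gives 37% and 16% in the 40% row. Nothing in the article makes the 50% an untreated rate, so I do not use those figures.
- **Targeting is not shown.** Treatment follows perceived risk by definition, and Study methods says that decisions rest on clinical judgement and routine laboratory results. That this tracks the abnormality under test is plausible only.
- **Excluding prophylaxis is defensible.** The article's argument for the composite concerns bleeding that has begun. Leaving prophylaxis out keeps clinicians' opinion out of the outcome, and bleeding despite prophylaxis still counts. This stands as a reason for the rule, but it does not remove the attenuation.
- **Sensitivity analyses may be in an analysis plan not shown.** That is fair, and their absence from the article is not the point. The point is the rule that the article states and its conflict with the Abstract.

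**Conclusion.** The concern holds in a limited form. The two descriptions of the primary outcome contradict each other on children treated for perceived risk, and this needs no assumption to establish. Under the Primary outcomes rule, attenuation of the objective 2 results follows if prophylaxis both works and is given more often to children with abnormal tests. Its size cannot be derived from the article. Under twofold targeting and a 30% to 50% reduction in bleeding, it ranges from slight (RR 1.46, power 71%, at 10% treated) to serious (RR 1.23, power 23%, at 40% treated).

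A reader might go further and conclude that the tests' predictive value will be masked, or that the 77% power claim is wrong. The article supports neither. The 77% reproduces under its own inputs, and the loss is zero if prophylaxis is ineffective. If prophylaxis is untargeted, the RR is unchanged.

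**What to change.** 1. State one primary definition, in the same terms, in the Abstract and in Primary outcomes.
2. Prespecify that the objective 2 logistic and ROC analyses of the sample 2 tests are repeated with non-routine prophylaxis coded the other way (counted as an event, if the Primary outcomes rule is kept). As a secondary check, repeat them with treated children excluded.
3. Report the number given non-routine prophylaxis by test result, so that readers can judge the share treated and its targeting.
4. Do not call a TEM parameter not useful on the primary coding alone where the alternative coding disagrees.
5. Treat covariate adjustment for prophylaxis as exploratory. Treatment lies between test and outcome, and clinician judgement influences both treatment and risk, so an adjusted estimate would be confounded.

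The cost is a few extra models on categories that the CRF already records. The exclusion analysis loses precision. At 40% treated with twofold targeting it keeps 60 × (1 − 0.615) ≈ 23 abnormal and 140 × (1 − 0.308) ≈ 97 normal children, with about 37% power even if the RR among them is 1.5. It should therefore not act as a veto.

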### Secondary outcomes

Secondary clinical outcomes will be collected for all intervals as follows:Red cell transfusion expressed as any vs. none and total red cell transfusion volume.FFP, platelet concentrate and cryoprecipitate transfusion expressed as any vs. none and total volume of each blood component.Non-blood component pro-haemostatic treatments (extra protamine, rFVIIa, any antifibrinolytic drug, fibrin sealant or fibrinogen concentrate) expressed as total dose per Kg body weight of each agent.Time from cessation of CPB to chest closure.Post-operative complications or death.

### Laboratory testing

Each blood sample will undergo parallel testing by:Thromboelastometry (ROTEM, Tem Innovations GmbH). Four different tests will be performed on this platform (INTEM, EXTEM, FIBTEM and HEPTEM tests using manufacturer's standard reagents). Each test will yield eight parameters; i) clot time (CT), ii) clot formation time (CFT), iii) alpha angle, iv) maximum clot firmness (MCF), v-vii) amplitude at 10, 20 and 30 min after CT and viii) lysis index at 30 min after CT.Reference laboratory tests. These tests will provide 10 measurements on each sample;Prothrombin time and activated partial thromboplastin timeFibrinogen activity (Clauss assay)Anti-Xa assay (heparin activity)Endogenous thrombin potential ((ETP); thrombin generation assay in plasma)Platelet countPlatelet function testing by whole blood electrical impedance aggregometry (Multiplate, Roche Diagnostics) with the Adenosine diphosphate (ADP-test), Thrombin Receptor Activating Peptide (TRAP-test) and Collagen (COLL-test) standard manufacturer's reagents. The platelet function test results will be expressed as area under curve, lag time and amplitude.

### Sample size calculation

The study size is 200 participants with blood samples taken. In estimating the power of the study and precision of the estimates, we have assumed that the rate of the primary outcome is 50 % in this population. Additionally, we have considered two alternative estimates of prevalence of blood clotting abnormalities (30 % and 5 %) in the study population:

**Objective 1** (describing the prevalence of different blood clotting abnormalities in the population): a sample size of 200 participants will allow a prevalence of 30 % to be estimated with a 95 % confidence interval of +/− 7 % (23.7 %, 36.9 %) and a prevalence of 5 % to be estimated with a 95 % confidence interval of +/− 4 % (2.4 %, 9.0 %).

**Objective 2** (estimating the extent to which TEM and reference laboratory test results predict clinical concern about bleeding): the power to estimate a relative risk of a given magnitude is dependent on the prevalence of the blood clotting abnormalities and increases with increasing prevalence. The study will have a minimum of 77 % power to estimate a relative risk of 1.5, given a rate of blood clotting abnormalities of >30 % in the population and >80 % power to estimate a relative risk of 2, given a rate of blood clotting abnormalities of between 4 % and 5 %.

**Objective 3** (estimating diagnostic accuracy of TEM test results vs. reference test results): a sample size of 200 participants will allow the sensitivity and specificity of each TEM test result to identify defined blood clotting abnormalities with a prevalence of 30 % to be estimated with a 95 % confidence interval of +/− 10 % (79.5 %, 96.2 %) for a sensitivity of 90 % increasing to +/−13 % (46.5 %, 72.4 %) for a sensitivity of 60 %. The specificity will be estimated with a 95 % confidence interval of +/−6 % (83.8 %, 94.4 %) for a specificity of 90 % increasing to +/−9 % (51.4 %, 68.2 %) for a specificity of 60 %. For a prevalence of 5 %, the 95 % confidence intervals are +/− 35 % (55.5 %, 100 %) for a sensitivity of 90 % and +/−35 % (26.4 %, 87.8 %) for a sensitivity of 60 %. The corresponding figures for specificity are +/− 5 % (84.8 %, 93.9 %) for 90 % specificity and +/− 7 % (52.7 %, 67.0 %) for 60 % specificity.

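### Objective 2 power: the 77% is not a floor for every prevalence above 30%; power peaks near 40% prevalence and falls below 77% above about 50%

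*Protocol article*

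**What the plan says.** The Sample size calculation in the protocol article fixes the number of children ("The study size is 200 participants with blood samples taken") and the outcome rate ("we have assumed that the rate of the primary outcome is 50 % in this population"). It plans for two prevalences of a clotting abnormality, 30% and 5%.

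For Objective 2 it says that the power for a given relative risk "is dependent on the prevalence of the blood clotting abnormalities and increases with increasing prevalence". It then claims a "minimum of 77 % power to estimate a relative risk of 1.5, given a rate of blood clotting abnormalities of >30 % in the population". No upper limit is attached to that prevalence. The companion claim for a relative risk of 2 is bounded on both sides: ">80 % power to estimate a relative risk of 2, given a rate of blood clotting abnormalities of between 4 % and 5" per cent. The test, the significance level and the sidedness are not stated.

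**The concern.** When the total is fixed, the prevalence of the abnormality decides how the 200 children divide into those with it and those without. Power improves as the split becomes more even and worsens again as the group without the abnormality shrinks. It therefore cannot keep rising with prevalence, and a value calculated at 30% need not be the lowest value above 30%.

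The true prevalence is unknown. Estimating it is Objective 1, the Statistical analyses section derives the categories of abnormality from the data, and one of the two samples is taken after bypass. If an abnormality proves common, a reader who takes the text at its word will believe that at least 77% power stood behind a finding of no association, when the design had less.

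**Working it through.** **Inputs**

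- N = 200, overall outcome rate 50%, relative risk (RR) 1.5 or 2: all from the Sample size calculation.
- Two-sided 5% level: assumed, because none is stated. It agrees with the 95% confidence intervals used elsewhere in that section.

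**Formulas**, for prevalence π:

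- group sizes n1 = 200π (abnormal) and n0 = 200 − n1 (normal)
- outcome risks p0 = 0.5 / (1 + π(RR − 1)) and p1 = RR × p0, which keep the overall rate at 50%
- difference d = p1 − p0; continuity correction c = 0.5(1/n1 + 1/n0)
- null standard error s0 = √[0.25(1/n1 + 1/n0)]; alternative standard error s1 = √[p1(1 − p1)/n1 + p0(1 − p0)/n0]
- power = Φ[(d − c − 1.96 s0)/s1]

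**Step 1: reproduce the stated figures**

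RR 1.5, π = 30%: n1 = 60, n0 = 140, p0 = 0.5/1.15 = 0.435, p1 = 0.652, d = 0.2174, c = 0.0119, s0 = 0.0772, s1 = 0.0744. The argument of Φ is (0.2174 − 0.0119 − 0.1513)/0.0744 ≈ 0.73, so power is 76.7%, against 77% stated.

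RR 2: 79.0% at π = 4%, 80.9% at 4.1% and 91.6% at 5%, which matches the claim of more than 80% between 4% and 5%.

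Other choices at π = 30% and RR 1.5 miss the 77%: 81.3% without continuity correction, 80.0% with Fisher's exact test, 79.5% on the log odds ratio. Taking 50% as the risk in children without the abnormality gives 92.4% uncorrected and 89.7% corrected. Of the variants tried, only the corrected test with a 50% overall rate reproduces both stated powers.

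**Step 2: move prevalence above 30%, RR 1.5**

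| Prevalence | n1 / n0 | p1 vs p0 | Power, corrected | Power, uncorrected |
|---|---|---|---|---|
| 30% | 60 / 140 | 0.652 vs 0.435 | 76.7% | 81.3% |
| 40% | 80 / 120 | 0.625 vs 0.417 | 78.9% (peak) | 82.9% (peak) |
| 50% | 100 / 100 | 0.600 vs 0.400 | 77.1% | 81.2% |
| 55% | 110 / 90 | 0.588 vs 0.392 | 74.9% | 79.3% |
| 60% | 120 / 80 | 0.577 vs 0.385 | 71.6% | 76.4% |
| 70% | 140 / 60 | 0.556 vs 0.370 | 61.5% | 67.4% |
| 80% | 160 / 40 | 0.536 vs 0.357 | 45.2% | 52.5% |

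At 30% and 70% the group sizes are mirror images, so c and s0 are identical. The difference in risk is smaller at 70% (0.185 against 0.217) because the overall rate is held at 50%. The argument of Φ becomes (0.1852 − 0.0119 − 0.1513)/0.0752 ≈ 0.29, which gives 61.5%.

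With the reproducing formula, power is at least 77% only for prevalences of about 31% to 50%. Allowing 76.5% to round to 77% extends the upper end only to about 51%.

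**Step 3: does the shape depend on the method?**

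Uncorrected, the curve also peaks near 40% and drops below 77% above about 59%. If 50% is read as the risk in children without the abnormality, power peaks at about 50% prevalence and falls to 55% (corrected) or 65% (uncorrected) at 90%. Every version rises and then falls.

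**The case against.** The strongest reply is that the sentence is true over the range the authors planned for. Between 5% and 30% prevalence, power for RR 1.5 does rise (corrected: 19% at 5%, 42% at 10%, 68% at 20%, 76.7% at 30%), and it goes on rising to about 40%. Read as an explanation of how the two scenarios differ, it is sound. That stands, and it is why the sample size is not in question. It does not rescue the text, which states the trend without limit and applies its minimum to everything above 30%, while the RR 2 claim beside it is bounded.

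Three further points have some force:

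- The document gives no figure showing that any one abnormality affects more than half of the children, and separate types will each be less common than any abnormality at all. A high prevalence is therefore an assumption. The document nonetheless makes its own claim for that range.
- The shortfall is small at first: about 2 points at 55% and 5 at 60%. It becomes large only at 70% to 80%.
- The crossing near 50% belongs to the continuity-corrected test, which is inferred from its match to the stated figures.

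It is also fair that Objective 2 is framed as estimation, with logistic regression and ROC analyses, so a two-group power figure is only a rough guide. That limits the consequence but does not make the figure right.

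**Conclusion.** The concern holds. The 77% is correct at 30% prevalence, and the statement about rising power is correct up to about 40%. The unlimited trend and the open-ended minimum are wrong. With the calculation that reproduces the protocol's own figures, the floor fails above about 50% prevalence, by roughly 15 points at 70% and 32 points at 80%.

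These figures assume a two-sided 5% level, a 50% overall outcome rate and a continuity-corrected test. The exact crossing point depends on those choices, but the eventual fall in power does not. No design or analysis decision changes. What changes is how much weight a null association may carry if an abnormality turns out to be common.

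**What to change.** In the Objective 2 paragraph, remove the general statement that power rises with prevalence and the word minimum. A replacement could read: *Assuming an overall outcome rate of 50% and a two-sided 5% continuity-corrected comparison of two proportions, power for a relative risk of 1.5 is 77% to 79% for prevalences of about 30% to 50%, and falls to 72% at 60%, 62% at 70% and 45% at 80%.* The authors should confirm the test and significance level they used; if either differs, the figures should be recalculated with it. A shorter alternative is to bound the existing claim at about 30% to 50% and say that power is lower beyond that.

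The cost is one sentence and a less favourable stated power for common abnormalities. The sample size stays at 200.
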